**12.10 General assessment of each study subject during and after the study**

The principle investigator should give -based on his clinical experience and knowledge about the respective study parameters of each study subject- his personal opinion on the anthropometrical development of the infant as well as the acceptance and tolerance of the respective study formula by filling in a general assessment form (see annex) after 4, 6 and 12 months of each study subject's age. If an infant finishes the observation period before the regular end of the individual study period the form has also to be filled in as final assessment.

**12.11 Provision of formulas**

At study entry mothers and their infants in the formula groups receive adequate amounts of respective infant formula powder to cover the first study period, i.e. for the next 2-4 weeks. Afterwards, the packages needed to cover the next study period of 4-8 weeks will be delivered to the participating families by the health visitors on the occasion of planned home visits or will be given to the mothers when coming to planned examinations of the study.

**12.12 Study schedule overview**

The planned schedule is depicted in the following table.

| Age of infant (w)               | 0 - <8   | 8      | 10 | 12    | 14 | 16     | 18 | 20    | 22 | 24     | 26 | 28    |
|---------------------------------------------|----------|--------|----|-------|----|--------|----|-------|----|--------|----|-------|
| Personal contact (clinic / home visit)      | X (U2/3) | X      |    |       |    | X (U4) |    |       |    | X (U5) |    |       |
| Interview (home visit or telephone contact) |          |        | X  | X     | X  |        |    | X     |    |        |    | X     |
| Examination day                             | 1        | 2      |    |       |    | 3      |    |       |    | 4      |    |       |
| Informed consent                            | X        |        |    |       |    |        |    |       |    |        |    |       |
| Randomization                   | X        |        |    |       |    |        |    |       |    |        |    |       |
| Clinical examin.                            | X        | X      |    |       |    | X      |    |       |    | X      |    |       |
| Basal questionnaire                         | X        |        |    |       |    |        |    |       |    |        |    |       |
| Follow-on quest.                            |          | X      | X  | X     | X  | X      |    | X     |    | X      |    | X     |
| General assessment by the PI                |          |        |    |       |    | X      |    |       |    | X      |    |       |
| Special recheck of feeding group            |          | X (FF) |    |       |    | X (BF) |    |       |    |        |    |       |
| Vaccination with HEXAVAC        |          | D      |    | I; D  |    | D      |    | I     |    |        |    |       |
| Stool sample                    |          | X      |    |       |    | X      |    |       |    | X      |    |       |
| Blood sample                    |          |        |    |       |    |        |    |       |    | X      |    |       |
| Formula provided                | IF       | IF     |    | IF    |    | IF     |    | IF    |    | FOF    |    | (FOF) |
| Age of infant (w)               | 30       | 32     | 34 | 36    | 38 | 40     | 42 | 44    | 46 | 48     | 50 | 52    |
| Personal contact (clinic / home visit)      |          |        |    |       |    |        |    |       |    |        |    | X     |
| Interview (home visit or telephone contact) |          | X      |    | X     |    | X      |    | X     |    | X      |    |       |
| Examination day                             |          |        |    |       |    |        |    |       |    |        |    | 5     |
| Clinical examin.                            |          |        |    |       |    |        |    |       |    |        |    | X     |
| Follow-on quest.                            |          | X      |    | X     |    | X      |    | X     |    | X      |    | X     |
| General assessment by the PI                |          |        |    |       |    |        |    |       |    |        |    | X     |
| Special recheck of feeding group            |          |        |    |       |    |        |    |       |    |        |    |       |
| Vaccination with HEXAVAC        |          |        |    |       |    |        |    | I; D  |    |        |    |       |
| Stool sample                    |          |        |    |       |    |        |    |       |    |        |    | X     |
| Blood sample                    |          |        |    |       |    |        |    |       |    |        |    | X     |
| Formula provided                |          | FOF    |    | (FOF) |    | FOF    |    | (FOF) |    | FOF    |    |       |

 time window of 1 week e.g. 12 weeks = 12th weeks; 16 weeks = 16th weeks     formula groups only

 subgroups (specific written informed consent)     NL & CH according to country specific regulations

IF infant formula, FOF follow on formula, FF formula feeding, BF breastfeeding

## **13. DATA AND SAMPLE COLLECTION AND LABORATORY ANALYSES**

### **13.1 Number of febrile episodes (primary outcome parameter)**

The primary outcome parameter, i.e. the number of febrile episodes (peak rectal temperature at least 38.5 °C) in healthy term born infants during the first year of life will be assessed by structured interviews recalling data filled in by the mother in a diary with record cards and afterwards checked against the general practice records.

### **13.2 Symptoms of illness (secondary outcome parameter)**

Symptoms of illness (cough, wheeze, runny nose, vomiting, diarrhoea, others) indicating a viral or bacterial infection are recorded by the mothers by filling in prepared diaries and are recalled by interviews during the 2-4 weekly personal or telephone contacts. Information on duration of symptoms and related medication, resulting absence from day care or even hospitalisation etc. will be collected as well.

### **13.3 Faecal parameters (secondary outcome parameter)**

For each examination day, a stool sample of approximately 2-5 g faeces will be collected into stool containers provided by NUMICO Research and stored at -20°C for later analysis. The microbial composition of the faecal samples will be tested in those samples in selected subgroups directly by fluorescent in situ hybridisation (FISH) using specific 16S rRNA-targeted oligonucleotide probes for e.g. *Bifidobacteria*, *Lactobacilli*, *Bacteroides*, *E. coli* and *Clostridia*. Amounts are expressed as percentage of the total number of bacteria. FISH analyses will be organised by NUMICO Research.

As further faecal parameters of gut health and immune status, faecal pH will be measured and faecal antibodies (sIgA) determined with standard laboratory techniques (Elisa, FACS, RT-PCR).

### **13.4 Plasma parameters (secondary outcome parameter)**

At examination days 4 and 5, i.e. at the infants' age of 6 and 12 months, 2-3 ml venous blood will be obtained for analysis of immune status from those infants whose parents agreed to participate in study subgroups providing blood samples of the infants during the study. Immediately after blood sampling, the blood cells will be separated, prepared and stored at -20°C stored for later analysis of different blood cells and subpopulations. The remaining plasma will be stored frozen till later analysis of plasma antibodies by ELISA technique. All analyses will be organized by NUMICO in collaboration with the centers.

Following parameters will be investigated:

- Plasma antibodies: IgG, IgE, specific antibodies (response to vaccination / allergy markers: antibodies against cow's milk, cat, soy, wheat, dust mite allergens)
- Lymphocyte subpopulations
- Cytokines (after ex vivo stimulation)

As most of the study parameters will be influenced by infectious disease and/or anti-biotic treatment, stool and blood samples should be only obtained after a period of two weeks free of infectious symptoms and/or antibiotic treatment. To fulfil this requirement, it is allowed to postpone the sampling for a maximum of two weeks.

### **13.5 Allergy symptoms (secondary outcome parameter)**

The clinical examinations of the infants will include also the assessment of allergic symptoms with focus on the skin.

Occurrence and severity of atopic dermatitis will be assessed using the SCORAD index (The European Task Force on Atopic Dermatitis. Consensus Report of the European Task Force on Atopic Dermatitis: severity scoring of atopic dermatitis, the SCORAD index. *Dermatology* 1993; 186:23-31; Oranje AP, Stalder JF, Taieb A, Tas-set C, De Longueville M. Scoring of atopic dermatitis by SCORAD using training atlas by investigators from different disciplines. *Pediatr Allergy Immunol* 1997; 8:28-34).

The skin will also be checked during this examination for eczema and urticaria as well as other symptoms.

### **13.6 Anthropometrics and other safety parameter**

Growth parameters (for birth retrospectively collected) will be measured as part of the clinical assessment at study entry and at the infants' age of 2, 4, 6 and 12 months (study end) with standardized techniques: The naked infants are weighted on an electronic scale accurate to 1 g. Recumbent length is measured on a Harpenden stadiometer to the nearest 1 mm (one examiner holds the child's head and applies gentle pressure to bring the top of the head into contact with the fixed headboard; the second examiner extends the child's legs and, applying gentle traction, brings the movable footboard to rest firmly against the child's heels with the toes pointing directly upward). The occipital-frontal head circumference is measured using a paper or plastic tape measure or a flexible narrow steel tape to the nearest 1 mm (the tape is applied firmly around the head above the supraorbital ridges, covering the most prominent part of the frontal bulge anteriorly, and over the part of the occiput that gives maximum circumference). As indicator of body composition (regional fat and fat-free tissue), mid-upper arm circumference will be measured with a non-stretchable tape at the midpoint between the acromium and olecranon to the nearest 1 mm; triceps and subscapular skinfold thickness will be examined by means of a Holtain skinfold caliper calibrated to 0.2 mm. Only experienced personnel will perform the measurements. At any time, 3 measurements are taken for each growth parameter and the average value will then be considered. Actual chronological decimal age is used to calculate the standardized anthropometric indices (z scores). The z scores represent the distance in standard deviation (SD) units from reference growth values adjusted for age and gender derived from the Eurogrowth study (Haschke F, van't Hof MA, and the Euro-Growth Study Group. Euro-Growth References for length, weight, and body circumferences. *J Pediatr Gastroenterol Nutr* 2000, 31(suppl 1) S14-38).

Aside from the anthropometrical development of the infants, safety data on the incidence of gastrointestinal discomfort (flatulence / cramps / colics; occurrence of nappy rash) as well as on formula acceptance and tolerance (number of feedings / intake; spitting up / possetting / vomiting; stool frequency / stool consistency / stool colour) will be collected by the structured interviews throughout the study period.

Safety is also defined as absence of *unanticipated*\* adverse effects compared to baseline (pre-treatment) or “normal” conditions as indicated by the control group. All *unanticipated* adverse events encountered during the study after treatment has started, whether considered related to treatment or not, will be reported on the subject’s record: intensity, relationship to test substance, action taken regarding test substance, and outcome to date (see Unanticipated Adverse Event Report Form the annex). Such preliminary reports will be followed by detailed descriptions when available.

*Unanticipated serious*\* adverse events thought to be associated with the study feeding will be reported to NUMICO Research Germany within 24 hours (Telefax [name], Telephone [name] [name]).

NUMICO Research has effected an insurance in connection with this study which meets the requirements as established, e.g., by the “De Nederlandse Wet Medisch Wetenschappelijk Onderzoek met Mensen”.

---

\* *Unanticipated adverse events* are defined as any event, the specificity or severity of which is not consistent with those known from the risk information in the consent form (e.g. for blood samplings) or are reasonably expected to accompany the natural history and progression of the subjects’ condition throughout the study.

*Serious adverse events* are generally defined as events that result in any of the following outcomes: death, a life threatening experience; inpatient hospitalisation or prolongation of existing hospitalisation; a persistent or significant disability/incapacity; or a congenital anomaly/birth defect. In addition, events that may not result in death, be life-threatening, or require hospitalisation may be considered serious when, based upon appropriate medical judgement, they may jeopardise the subject and may require medical or surgical intervention to prevent one of the outcomes listed above.

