| MAIN PARAMETERS OF SAFETY | 
Absence of unanticipated adverse events with special focus on
 
 
• Incidence of gastrointestinal discomfort
 
• Anthropometric parameters
 
• Acceptance and tolerance
 
                                                                                                                                                                                                                                                                                                                                                                                                                                                                                                                                                                                                                                                                                                                                                                                                                                                                                                                                                                                                                                                                                                                                                                                                                                                                                                                                                                                                                                                                                                                                                                                                                                                                                                                                                                                                                                                                                                                                                                                                                                                                                                                                                                                                                                                                                                                                                                                                                                                                                                                                                                                                                                                                                                                                                                                                                            |

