### 6.2 Secondary outcome parameters

As secondary outcome parameters symptoms of illnesses indicating a viral or bacterial infection (cough, wheeze, runny nose, vomiting, diarrhoea, others) as recorded in the diaries of the mothers.

The definition of such symptoms is as follows

- *Cough*: sudden expulsion of air from the lungs with a noise that clears the air passages
- *Wheeze*: breathing with an abnormal (e.g. husky or whistling) sound mostly due to difficult respiration by narrowed airway passages
- *Runny nose*: nasal discharge of any mucus-like material coming out of the nose (Rhinorrhea)
- *Vomiting*: forcing the contents of the stomach up through the esophagus and out of the mouth
- *Diarrhoea*: at least three loose-to-watery bowel movements in a 24 h period that exceeded the child's usual daily stool frequency by two or more stools and perceived as diarrhoea by the mother (WHO definition: "passage of loose or watery stools at least three times in a 24 h period"; emphasis on importance of change in stool consistency rather than frequency; usefulness of parental insight in deciding whether children have diarrhoea or not; see WHO: The treatment of diarrhoea: a manual for physicians and other senior health workers, WHO/CDR/95-3. Geneva: World Health Organisation, 1995)

Severity of illness episodes is explored by means of parameters such as

- Duration of illness symptoms (number of days; illness period is considered as finished if the child is again without symptoms and shows a normal activity level; after recovery, another illness is considered as new period if the symptoms occur at least three days after the stated time of recovery from a previous episode).
- Medication required as therapy (paracetamol, antibiotics, others) and their duration of use (number of days)
- Number of visits to hospital/practitioner
- Information if a physician has been visited who confirmed a diagnosis of infection
- Absence from day-care due to illness (number of days)
- Necessity of hospitalisation and respective duration (number of days)

Occurrence of allergic symptoms with focus on the skin (atopic dermatitis) will be checked during the clinical examinations:

- Criteria for diagnosis: typical morphology and distribution, pruritus (sign of scratching), chronicity (duration at least 14 d and/or chronically relapsing)
- Severity to be scored according to SCORAD

The skin should also be checked during this examination for eczema and urticaria.

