The principle investigators will be responsible for conducting the study in accordance with the approved protocol and will ensure that the provided feeding will be administered only to subjects entering the study and under his personal supervision or under the supervision of the pre-designated investigators responsible to them, and will not be supplied to any other investigator or to any clinic for feeding to subjects.

Together with the local co-clinicians they will be responsible for preparing and maintaining adequate case histories designed to record observations and other data pertinent to the study. Copies of the signed CRFs will be forwarded to the local NUMICO Research monitor. If data are already fed into a computer, a copy of the data set should be handed over, too. After evaluation and common discussion of all study results the principle investigators will prepare a final report (alternatively one or more publications may be prepared).

All study related effects reported by the physician, dietician, nurse, or by the parents will be recorded and the local supervising physicians will pass details of all *unanticipated*\* untoward effects to NUMICO Research Germany. The nature of each unanticipated adverse experience, time, and relationship to the feeding should be established. Those of *serious* nature\* thought to be associated with the study feeding will be reported to NUMICO Research Germany within 24 hours (NUMICO Research Germany, [name], [contact], Telefax [name]). The study can be interrupted by the clinicians at any time if any unforeseen problems arise. However, NUMICO Research Germany will be informed within 24 hours about any intention to unblind a study subject or to interrupt/discontinue the study (if possible before final measures are taken).

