## 19.2 Responsibility of NUMICO Research Germany

NUMICO will provide

- the appropriate agency clearance for the study (if necessary),
- the investigational products, appropriately labelled and packed,
- the randomisation schedule,
- the code envelope for unblinding of the trial material –if needed,
- the CRFs for recording all findings relevant for assessment of the selected parameters,
- financial remuneration for time and services as agreed upon according to the separate financial agreement.

All data transmitted to NUMICO Research Germany will be stored adequately.

---

\* *Unanticipated adverse events* are defined as any event, the specificity or severity of which is not consistent with those known from the risk information in the consent form (e.g. for blood samplings) or are reasonably expected to accompany the natural history and progression of the subjects' condition throughout the study.

*Serious adverse events* are generally defined as events that result in any of the following outcomes: death, a life threatening experience; inpatient hospitalisation or prolongation of existing hospitalisation; a persistent or significant disability/incapacity; or a congenital anomaly/birth defect. In addition, events that may not result in death, be life-threatening, or require hospitalisation may be considered serious when, based upon appropriate medical judgement, they may jeopardise the subject and may require medical or surgical intervention to prevent one of the outcomes listed above.

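### The 24-hour report covers only serious events the site judges both unanticipated and feeding-related; other deaths and hospitalisations have no reporting deadline, and the definition of unanticipated is garbled

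*Protocol*

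**What the plan says.** Section 13.6 sets two rules. The recording rule covers unanticipated "adverse events encountered during the study after treatment has started, whether considered related to treatment or not, will be reported on" the subject's record, so relatedness plays no part in it. The expedited rule is narrower: unanticipated serious "adverse events thought to be associated with the study feeding will be reported to NUMICO Research Germany within 24 hours".

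Section 19.1 repeats the expedited rule for serious events "thought to be associated with the study feeding will be reported to NUMICO Research Germany within 24 hours". It also has a slower route: "and the local supervising physicians will pass details of all" unanticipated "untoward effects to NUMICO Research Germany". That route has no causality condition and no deadline.

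The footnotes to sections 13.6 and 19 list death and inpatient hospitalisation among the criteria for seriousness. They define an unanticipated event as one inconsistent in kind or severity with the risks in the consent form, and then continue "or are reasonably expected to accompany the natural history and progression of the" subjects' condition.

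The synopsis states the main safety parameter as "Absence of unanticipated adverse events with special focus on" gastrointestinal discomfort, anthropometry, and acceptance and tolerance. Section 6.2 lists, among the severity measures for illness, "Necessity of hospitalisation and respective duration (number of days").

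**The concern.** Two site judgements decide what happens after a serious event: whether it was expected, and whether the formula caused it. Neither is easy to make in this trial. Infection is the efficacy target, so an infection admission is the serious event most readily called expected. The clinicians are blinded (section 11.1) and the events are common in infancy, so a single case gives little ground for blaming or clearing the formula. Harm would appear as an excess in one group, not as a recognisable case.

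The earlier experience with acidic oligosaccharides cited in section 3.4 is 15 infants per group over the first two months and 27 per group over about four months. This trial plans about 500 per group, fed until one year of age. At stake are how soon the sponsor learns of deaths and admissions, and whether all centres report the same kinds of event.

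**Working it through.** No power, alpha or sample-size figure enters this point, and the plan states none to reproduce. The check is to follow a serious event through the rules.

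**Step 1: the expedited rule.** A report within 24 hours is required if the event is serious AND unanticipated AND thought associated with the feeding. Sections 13.6 and 19.1 agree on this. Seriousness alone triggers nothing.

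**Step 2: the four cases.** Here the footnote is taken in its presumably intended sense, in which expected events are not unanticipated.

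| Site's judgement of a serious event | Adverse-event record | Passed to sponsor as an adverse event | Deadline |
|---|---|---|---|
| Unanticipated, associated | Yes (13.6) | Yes (13.6, 19.1) | 24 hours |
| Unanticipated, unrelated | Yes (13.6) | Yes (19.1) | None |
| Anticipated, associated | Only under the general instruction in 19.1 to record study-related effects | Not required | None |
| Anticipated, unrelated | Not required | Not required | None |

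One case of four has a deadline, and two of four require no adverse-event report to the sponsor.

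**Step 3: what else carries the last two cases.**
- *Hospitalisation.* It is collected for every infant through diary and interview (6.2, 12.6, 13.2). Case report forms are completed, signed and copied after the infant's participation ends (15, 19.1). Infants enter by 8 weeks of age and stay until one year, so this period lasts at least 52 − 8 = 44 weeks. The copy documenting an admission soon after entry may thus be due only about 44 weeks later, or later still for an infant enrolled younger.
- *Death.* It ends participation, and section 18 asks for a written reason for non-completion, with no recipient or deadline. No specific route is stated.
- *Other contacts.* Section 19.3 lists four-monthly progress reports and monitoring at set inclusion counts, with no stated safety content. The other 24-hour trigger in 19.1 is an intention to unblind or to stop, not an event as such.

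**Step 4: the footnote.** Read literally, its two limbs are alternatives, and the second makes events expected from the natural course count as unanticipated. Read as presumably meant, the negation carries over and such events fall outside. Take an admission for gastroenteritis of ordinary severity. Under the literal reading it is recorded as an adverse event and passed on. Under the other reading, a site that regards it as part of a normal first year does neither. The causality condition on the 24-hour report is the same under both readings.

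**Step 5: the safety parameter.** If serious events judged expected occurred more often in one group, the count of unanticipated events could still be zero in both. The parameter as worded in the synopsis would then be met despite the imbalance.

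**The case against.** The strongest reply is that the sponsor is not kept in the dark, and much of it stands. A reader might infer that events are screened out before anyone outside the site sees them. Section 19.1 contradicts that for unanticipated events, which go to the sponsor whatever the view on causality: causality governs the speed of reporting, not whether it happens.

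A reader might also infer that a fatal infection judged unrelated escapes the adverse-event record. Section 13.6 records unanticipated events regardless of relatedness, and a death in a healthy term infant is hard to call expected in severity. What is missing for such a death is the deadline.

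Nor do the documents support saying that there is no other route at all. The synopsis asks for details of any illness that leads to a visit, parents are interviewed every two to four weeks, and hospitalisation is a secondary outcome. Gastrointestinal discomfort, tolerance and growth are collected for every infant (13.6), so naming discomfort as a focus of unanticipated events is loose wording that loses no data. Section 13.6 says only that safety is *also* defined through unanticipated effects, so this is one safety parameter among several.

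Finally, section 19.1 binds investigators to local law and the Declaration of Helsinki, and the report form in the annex is not shown and may carry wider instructions. These points narrow the concern. They do not supply a deadline or settle the footnote.

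**Conclusion.** The concern holds in a limited form. As written, one of four combinations of expectedness and relatedness gives a serious event a reporting deadline. Unanticipated events judged unrelated reach the sponsor without one. Those judged anticipated need no adverse-event report, and the footnote leaves it open which events those are. The causality condition is certain on the text. The reach of the expectedness condition depends on how a centre reads the footnote, and the conclusion assumes that the unseen form sets no broader rule.

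The number of events affected cannot be derived, because the protocol gives no rates of hospitalisation or death. A reader might infer that reporting all serious events would reveal an imbalance between groups during the trial. The documents do not support that: it would need someone to compare events by group while the trial runs, and neither the present rule nor the change below provides this. The gain is prompt, uniform and complete reporting, and a safety parameter that reflects serious events of every kind. The primary analysis and the power are unaffected.

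**What to change.** - **Sections 13.6 and 19.1:** require all serious adverse events, whether or not anticipated and whether or not thought related, to be reported to the sponsor within the existing 24 hours on the existing form. Keep expectedness and relatedness as fields on that form, not as conditions for sending it.
- **Footnotes in sections 13.6 and 19:** reword the natural-history clause so that it has one meaning, identical in both places.
- **Synopsis and section 13.6:** state the safety parameter as the incidence of serious adverse events by randomised group, in place of the absence of unanticipated ones. The layout of the tables can be left to the analysis plan.

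The cost is protocol wording and some more reports, mostly routine infant hospitalisations. No visits, samples or new forms are needed.
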